## Abstract

**Background:**

A Just-in-Time Adaptive Intervention (JITAI) recognizes the dynamic nature of individuals’ states and contexts, predicts support needs, and sends tailored support at more opportune, actionable times.

**Objective:**

This paper outlines the application architecture and protocol for the pilot “Walking With Just-in-Time Adaptive Interventions” (WWJ) study, which uses a JITAI approach to improve walking behavior—duration, speed, and distance—and reduce stationary time, defined as idle sitting or standing.

**Methods:**

This study targets 20 adults who are physically inactive and leverages the Apple Watch to deliver fully automated tailored intervention notifications to “walk faster,” “walk longer,” or “stand up and move around” based on real-time data and contextual factors, including time-of-day activity patterns, geographic locations (eg, home, work, park, and gymnasium), weather conditions (eg, precipitation, wind speed, and humidity), and receptiveness. The protocol involves a preintervention assessment of demographics, behavior change constructs, anthropometrics, and resting vital signs; a 2-week observation period to establish walking behavior and stationary time baselines; a 2-week just-in-time learning period to evaluate receptiveness to untailored prompts at all applicable times; the 2-week JITAI intervention phase; and a postintervention assessment. Feasibility will be evaluated through protocol fidelity, participant adherence, Apple Watch wear-time compliance, user burden, acceptability ratings, and perceptions of benefits and preferences.

**Results:**

The WWJ architecture development began in spring 2021 and concluded in fall 2022. Participant recruitment and enrollment began in fall 2022. A total of 18 participants were recruited. Upon completion of the analyses, the results of this study are expected to be submitted for publication.

**Conclusions:**

Distinctively, the WWJ just-in-time learning period aims to train the learner based on user receptiveness within contexts by sending interventions whenever a participant meets the predetermined thresholds regardless of the likelihood that the user will be receptive to the notification to prune out nonopportune or “nonactionable” times. This approach may allow for greater customization during the JITAI period.

**International Registered Report Identifier (IRRID):**

DERR1-10.2196/79022

## Introduction

### Background

Regular physical activity (PA) participation attenuates the accumulation and progression of cardiometabolic risk factors such as hypertension, dyslipidemia, overweight and obesity, and insulin resistance that contribute to cardiometabolic disease morbidity and mortality [1,2]. PA, broadly defined as “any bodily movement produced by skeletal muscles that results in energy expenditure,” [3] is characterized by 4 dimensions: duration, frequency, intensity or rate of energy expenditure (EE), and PA type [3]. Historically, the 2007 American Heart Association Guidelines for Americans suggested adults 18-65 years of age should participate in moderate-intensity physical activity (MPA) for a minimum of 30 minutes per day for 5 days per week, including only intermittent bouts lasting 10 or more minutes [4]. The 2020 World Health Organization (WHO) recommendations build upon these guidelines, suggesting that the participation in 150-300 minutes of weekly MPA, 75-150 minutes of weekly aerobic vigorous-intensity physical activity, or an equivalent weekly combination of aerobic moderate-to-vigorous-intensity physical activity (MVPA) can be accumulated in bouts which can be of any length [5]. This approach allows for more flexibility in the accumulation of MVPA throughout each day, in which each minute counts toward weekly participation [5]. Nonetheless, a substantial proportion of adults—approximately 30% worldwide and 42% in high-income Western countries—fail to achieve these MVPA recommendations [6].

Moreover, a 2018 review found that adults spend approximately 8 hours participating in sedentary behavior (SB) daily [7]. SB is characterized by EE less than or equal to 1.5 metabolic equivalents of task (MET), with the Sedentary Behavior Research Network further detailing in 2017 that SB occurs while in a seated, reclined, or lying posture [8]. Emerging evidence indicates that excessive SB participation is associated with an increased prevalence of cardiometabolic diseases and risk of all-cause mortality [9] while reducing SB participation and subsequently increasing PA participation—even to a light-intensity—can significantly improve BMI and diastolic and systolic blood pressure (BP) [10-12]. Additionally, while intermittent standing bouts may be a feasible approach to reduce prolonged sitting, reclining, or lying through a postural change, passive or “idle” standing produces limited bodily movement, typically remaining below the 1.5 MET threshold to classify as light-intensity physical activity (LPA) [13].

Thus, reducing stationary behavior (ie, SB and idle standing) is a public health challenge that should be addressed through movement behaviors that reach MET thresholds at or above an LPA level. While specific LPA guidelines have yet to be established, the WHO advises adults to minimize SB time and substitute that time with any type and intensity of PA, including LPA [5]. Given that walking is generally feasible and accessible for adults who ambulate [5,14], it can serve as an ideal mode for not only replacing stationary behavior with LPA participation but also meeting WHO MVPA recommendations [5,14,15]. Walking paces around 0.82-0.89 m/s can exceed the 1.5 MET threshold for LPA [16,17]. To achieve the MPA threshold, walking must be performed at faster paces, typically around 1.3-1.8 m/s [16]. Since the 2020 WHO recommendations recognize that every minute of MVPA—regardless of bout duration—contributes toward an individual’s weekly targets [5], promoting walking behavior at faster paces may be an appropriate approach to increasing weekly MVPA volume while also breaking up stationary behavior.

### Mobile and Wearable Technology

Mobile and wearable technology advancements have unlocked innovative opportunities for collecting real-time walking and stationary behavior data and delivering individualized, theoretically driven, evidence-based interventions [18]. This technology can impact human behavior within “real-world” contexts by delivering actionable notifications based on real-time data collected from a user’s smartphone or wearable device [19,20]. A market-leading consumer-grade wearable—the Apple Watch (AW)—is equipped with a range of features for real-time data collection and notification interaction. Features include triaxial accelerometer, gyroscope, heart rate (HR), and GPS sensors that use Bluetooth to transmit and receive data and interact with other devices or cloud-based services. Notably, systematic reviews have supported the promising validity, reliability, sensitivity, and feasibility of leveraging the AW for assessing PA and SB [21,22]. Prior work has established that the AW can classify movement types (eg, sitting, lying, and walking) with moderate accuracy [20]. With the ability to dynamically detect behavioral and contextual variables in real-time and interact with users through immediate notifications, the AW is a feasible platform for delivering behavioral interventions, such as just-in-time and Just-in-Time Adaptive Interventions (JITAI), to increase walking behavior and decrease stationary time [19,20].

### Just-in-Time Intervention

According to the literature, a just-in-time behavioral intervention approach provides real-time support that is typically delivered through mobile or wearable applications or SMS text messaging or “texting” and is tailored to the user’s current behavioral, psychological, and physiological state using data via smartphone or wearable sensors [23,24]. This support typically encourages users to further engage in positive, goal-directed health behaviors or discourages them from further engaging in their current behaviors, such as prolonged SB [23,24]. Additionally, some just-in-time interventions have provided notifications only once daily, typically triggered at a preset time or event (eg, 10 AM or postgoal achievement), focusing mainly on summarizing past performance to motivate future behavior, rather than offering continuous or actionable notification [25,26]. The preprogrammed health and fitness notifications of the AW exemplify this approach by providing stand “reminders” or feedback—cuing users to move every 50 minutes if prolonged stationary behavior without at least a minute movement break was detected—and behavioral reinforcement through celebratory feedback messages when daily goals are met by closing the “move,” “exercise,” and “stand” rings which indicate aerobic EE, MVPA participation, and frequency of stationary breaks. Nevertheless, these notifications follow a rigid, predefined schedule or pattern rather than dynamically responding to the user and adapting to the various contextual influences that may impact their current behavior (eg, weather or geographic location) [24]. Thus, just-in-time interventions may have a limited impact on behavior change because they do not learn from and adapt to users’ states and their various contextual influences, remaining more prescheduled or reactive than predictive and personalized over time.

### About JITAI

To determine the most opportune moments for behavior change, JITAI approaches monitor changes in users’ behavioral, psychological, and physiological states, and environmental contexts over time to deliver support given the user’s state of need and receptivity to real-time actionable notifications [23,24]. This approach recognizes the dynamic nature of individuals’ states and contexts, requiring the system to predict (1) whether the person requires support, (2) the type or amount of support needed, and (3) whether or not the support will be acted upon [23]. A 2025 scoping review of JITAIs across several health behaviors (eg, PA, SB, fluid intake, and substance use) and settings revealed that while the included JITAIs were deemed feasible, a majority (N=62, 55%) of approaches solely relied upon self-reporting data, with few studies (21%) collecting passively monitored data via sensors in real time [27]. A 2019 systematic review of JITAIs specifically designed to promote PA and reduce SB participation revealed mixed evidence on their effectiveness [24], emphasizing notable feasibility concerns, such as low adherence and acceptability, and lack of a strong theoretical basis to guide the JITAI approaches or explain behavior changes. Reviews have highlighted the favorable use of the social cognitive theory and transtheoretical model (TTM) in the development and evaluation of mobile and wearable technology-based interventions for promoting PA and reducing SB [18,25,28,29]. To refine and optimize the effectiveness of the JITAI implementation for health behavior change, a thorough evaluation of the feasibility of the JITAI approach and the relevance of social cognitive theory and TTM behavior change constructs is warranted [18,24].

### Objective, Aims, and Research Questions

This protocol paper presents the development of the “Walking With Just-in-Time Adaptive Interventions” (WWJ) iPhone and AW app, server, and methodology for a 6-week pilot study among adults who are not meeting the 2020 WHO PA recommendations. The primary aims of the WWJ’s study are to examine the feasibility and initial impact of a 2-week JITAI approach for increasing walking behavior (ie, walking speed, distance, and duration) and decreasing stationary behavior (ie, duration of SB and idle standing) compared to a 2-week baseline observation period and a 2-week just-in-time learning period. Thus, our corresponding research questions include: (1) Is the WWJ feasible, regarding recruitment, retention, intervention fidelity, acceptability, adherence, and engagement? (2) To what extent does the just-in-time approach impact walking and stationary behavior compared to baseline? (3) How do changes in walking and stationary behaviors across a 2-week just-in-time and a 2-week JITAI approach compare to baseline?

## Methods

### Overview of Study Design

This pilot feasibility study will use a 1-way within-subjects repeated-measures design to examine changes in walking and stationary behaviors across the 3 time periods: baseline, just-in-time, and JITAI. This study will consist of a preintervention measurement session, followed by a 2-week observation period that will serve as a baseline for walking and stationary behaviors, a 2-week just-in-time learning period, a 2-week JITAI period, and concluding with a postintervention measurement session (Figure 1). The receptiveness-in-context data from the just-in-time learning period will be used to train and individually adapt the JITAI server by learning the ideal contexts in which the participants are most receptive to each of the 3 intervention notifications, as detailed in the Architecture of the WWJ App and Server section.

**Figure 1 figure1:**
[figure not shown]
CONSORT diagram: the WWJ study approach. CONSORT: Consolidated Standards of Reporting Trials; JITAI: Just-in-Time Adaptive Intervention; PAR-Q+: Physical Activity Readiness Questionnaire for Everyone; WWJ: Walking With Just-in-Time Adaptive Interventions.

### Participant Eligibility and Recruitment

A total of 20 participants will be recruited through community and clinical settings within a small city in New Castle County, Delaware, United States, using flyers, referrals, and social media (eg, Facebook and Instagram). Prospective participants will be directed to an online screening portal for the first screening phase (Figure 1) to determine study eligibility. Inclusion criteria will be adults aged 18-65 years, who own an Apple iPhone version 6s or newer, can speak and read in the English language, and self-report not achieving the minimum MVPA threshold of 150 weekly minutes in the previous week [5]. Exclusion criteria in the second screening phase will include answering “yes” to any general health and follow-up questions from the Physical Activity Readiness Questionnaire for Everyone, indicating that they are not cleared for PA participation without medical consultation and supervision [30]. If the screener indicates that a prospective subject is eligible, the informed consent form will be delivered to prospective participants via REDCap (Research Electronic Data Capture, Vanderbilt University).

### Architecture of the WWJ App and Server

The research team has previously detailed a comparable server and application development [19]. The WWJ fully automated multiagent system operated on a per-agent architecture comprising 4 modules—context analyzer, learner, executor, and communicator (Figure 2). In the WWJ agent-level design, learning the support need policy is framed as a fully supervised classification problem rather than as a Markov Decision Problem [31] to account for the time constraints of a 2-week baseline and 2-week just-in-time learning period and the AW’s battery-life constraints, which are particularly so when leveraging the HR sensor and GPS networks. Architecture development began in spring 2021 and concluded in fall 2022. Aligning with the CONSORT EHEALTH checklist (V.1.6.1), all updates to the WWJ application and server after this finalized development will be identified by date, version number, and description to allow for the replicability of the intervention [32].

**Figure 2 figure2:**
[figure not shown]
WWJ architecture per agent. AW: Apple Watch; WWJ: Walking With Just-in-Time Adaptive Intervention.

The context analyzer synthesizes external (eg, weather and calendar) and internal (eg, GPS coordinates mapped to tagged locations) contexts into a current context feature vector. At decision points, these contextual features (detailed under “contextual variables”) are used in binary classification models to determine whether an intervention notification should be sent based on the predicted likelihood of successful behavior change within these contexts as processed and interpreted by the learner module. Thus, 3 decision trees (policies) will be trained for each user corresponding to the intervention notification types (Figure 3)—walk faster (ie, “You should pick up the pace”), walk longer (ie, “Let’s make it a longer walk”), and stand up and move around (ie, “It’s time to move around for one minute”).

**Figure 3 figure3:**
[figure not shown]
The WWJ intervention notifications: walk faster, walk longer, and stand up. WWJ: Walking With Just-in-Time Adaptive Intervention.

The learner module (Figure 2) also establishes baseline walking and stationary behaviors during the initial 2-week observation period by passively monitoring behaviors and calculating their applicable averages (eg, average walking speed) per bout. During the just-in-time learning period, intervention notifications are triggered at each instance that participants meet a predetermined threshold for walking and stationary behaviors—unless they have marked themselves as “busy” on their calendar to not burden the user during unsuitable times such as work meetings. The threshold for the walking notifications is set at 250 m from the initial start point of a walking detection. This distance was chosen after trial-and-error field testing among 4 authors ([name], AV, KD, and [name]), which indicated that walking less than 250 m from a given starting location may not align with viable opportunities to walk faster or longer. The WWJ application will send a “walk longer” notification if the system recognizes that the user is in or near a previously tagged location. In all other cases, participants will receive a “walk faster” notification. When stationary behavior is detected for 30 continuous minutes, the application will send the “stand up and move around” notification. The system will determine if these interventions are successful or not (ie, receptiveness) either by comparing the current behaviors in the just-in-time learning period to those in the observation period within the same contexts for walking behavior or by the AW detecting that the user got up and walked around for a minute for stationary behavior. As shown in Figure 2, data collected by the executor during the just-in-time learning period serves as labeled training data to compute and optimize personalized prompting policies for the JITAI period. At the end of the just-in-time learning period, the learner module uses this labeled data to generate a decision-tree–based policy, predicting when and when not to send the intervention notifications to the user based on their current context, past receptiveness, and predicted support needs. As predicting behavior is uncertain, the learning model will deliberately use intervention notifications even if the user may not be receptive, with a 10% chance of such occurrences, to allow behavior change in previously nonoptimal contexts and for the system to learn continually.

The communicator module will ensure that data will flow seamlessly through connections between the AW and a paired iPhone, the iPhone and Cloud, and the Cloud to our central server for secure data storage, processing, and offline analysis. This transmission process will occur every 2 hours. This timeframe was chosen after the aforementioned trial-and-error field tests to maximize AW battery life. When the WWJ application is running on the AW, the main user interface displays the current behavior (stationary or walking), HR, and tagged location of the participant (Figure 4).

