##### Walking and Stationary Behaviors

Our WWJ app will collect timestamped walking and stationary behaviors once respective thresholds are met (described previously in the Architecture of the WWJ App and Server section). The Apple watchOS behavior detection APIs use its combined location sensors—the GPS, the Globalnaya Navigatsionnaya Sputnikovaya Sistema, Galileo, and Quasi-Zenith Satellite System—and its motion sensors—triaxial accelerometer and gyroscope—to detect walking and stationary behaviors via Apple’s proprietary algorithms. These walking behaviors will include duration to the nearest whole second, distance to the nearest meter, and speed calculated from the collected distance divided by duration to the nearest meter per second. In addition, when a walking bout is detected, HR will be collected every 10 seconds. The duration of stationary behavior will be recorded to the nearest whole second.

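### The walk-faster prompt fires at 250 m, but its success is compared with a per-bout average speed; unless recording starts at 250 m, unprompted walking attenuates the measured response, most in short walks

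*Protocol article*

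**What the plan says.** All references are to the protocol article.

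- **Trigger** (Architecture of the WWJ App and Server, text below the Figure 3 caption): "The threshold for the walking notifications is set at 250 m from the initial start point of a walking detection". A user who is not in or near a tagged location gets the walk-faster message.
- **Baseline** (same section): the learner module sets the baseline by "passively monitoring behaviors and calculating their applicable averages (eg, average walking speed) per bout".
- **Success rule** (same section): a walking prompt is judged by "comparing the current behaviors in the just-in-time learning period to those in the observation period within the same contexts for walking behavior". No measurement window or margin is given.
- **Speed** (Walking and Stationary Behaviors): "speed calculated from the collected distance divided by duration to the nearest meter per second". No segment after the prompt is defined.
- **Recording** (same section, first sentence): the app "will collect timestamped walking and stationary behaviors once respective thresholds are met".
- **Use of the label**: "data collected by the executor during the just-in-time learning period serves as labeled training data" for the decision trees (Architecture section). The success or failure of prompts is also a secondary analysis (Analytic Plan). Nonadherence to a prompt triggers a query about the reason (Feasibility), presumably on the same label.
- **Status** (Results): data collection was completed in 2024 and analyses are pending.

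**The concern.** The first 250 m of a prompted walk come before the prompt and cannot respond to it. If the speed being compared is the average over the whole walk, that stretch pulls the measured response toward zero. The pull is strongest when the walk ends soon after 250 m.

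The same label would train the walk-faster tree and supply the secondary result on prompt success. If walk length differs by place, time of day or weather, contexts with short walks could look non-receptive because of how speed is measured, and prompts there would be held back in the JITAI period. The reported success rate would also be too low.

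**Working it through.** The article gives no success rate or label-error figure, so there is nothing of its own to reproduce here.

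**Step 1: attenuation.** The 250 m trigger is from the article. Assumed: usual speed v0 throughout the first 250 m, speed v0(1+x) afterwards, total length D metres. Whole-bout time is 250/v0 + (D−250)/[v0(1+x)], so

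whole-bout speed ÷ usual speed = D / [250 + (D−250)/(1+x)].

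Example, x = 0.10 and D = 300: 300/(250 + 50/1.1) = 300/295.45 = 1.015.

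| D (m) | True +10% appears as | True +20% appears as |
|---|---|---|
| 300 | +1.5% | +2.9% |
| 400 | +3.5% | +6.7% |
| 500 | +4.8% | +9.1% |
| 1000 | +7.3% | +14.3% |

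This step needs no noise assumption. Scoring only the part after 250 m would show the full gain at every length.

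**Step 2: from attenuation to labels.** With no noise and a rule of simply being faster than baseline, every attenuated gain above is still positive and no label flips. False failures need noise, a margin or rounding. Assume success means faster than the baseline average, that this average is known without error, and that bout-to-bout noise is normal with SD equal to 10% of the mean. Then

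P(success) = Φ(apparent rise ÷ SD).

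A prompt with no effect scores 50%. For a true 10% gain, two noise assumptions for the segment after the prompt are compared: the same 10% SD whatever the length, or an SD that grows as the segment shortens, 10% × √[D/(D−250)].

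| D (m) | Whole bout | After 250 m, constant SD | After 250 m, SD growing as segment shortens |
|---|---|---|---|
| 300 | 56% | 84% | 66% |
| 400 | 64% | 84% | 73% |
| 500 | 68% | 84% | 76% |
| 1000 | 77% | 84% | 81% |

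The loss from whole-bout scoring is 28, 20, 16 and 7 percentage points under constant SD, and about 10, 9, 8 and 4 points under the length-dependent SD. Other assumed values with constant SD: for a 10% gain and SD 15%, the success rate falls from 75% to 54–69% over the four lengths; for a 20% gain and SD 10%, from 98% to 61–92%.

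**Step 3: rounding.** The article records speed to the nearest whole m/s. Taken literally, with an assumed usual speed of 1.2 m/s, a 10% gain (1.32 m/s) rounds to 1 under either scoring and disappears. A 30% gain (1.56 m/s) rounds to 2 after the prompt, but the whole-bout speed is 1.25 m/s at 300 m and 1.45 m/s at 1000 m, and both round to 1, the same as baseline.

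**The case against.** A reader might infer that the plan definitely scores whole bouts and that real successes are therefore labelled failures. The documents support neither step.

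- **Whole-bout scoring is an inference.** The sentence on collecting behaviors once thresholds are met can be read as recording from 250 m onward. Speed would then be post-250 m speed in both periods, which is the comparison recommended here. Two things favor the whole-bout reading. Data Processing aligns bout timestamps to compute transitions between states, which needs true bout starts. Recording from 250 m would also cut the first 250 m from the bout distance and duration outcomes in the Analytic Plan. These points make whole-bout scoring more likely but do not settle it.
- **Attenuation does not reverse a gain.** This stands in full. Any misclassification rate depends on an assumed rule, SD, gain and walk length.
- **A constant SD flatters post-prompt scoring.** This also stands, which is why both noise assumptions are shown.
- **Bout lengths are not reported.** That inactive adults take many walks only a little over 250 m is plausible but undocumented, as is any link between walk length and context.
- **A condensed article may omit the label formula.** An unstated window alone would not be a point. The issue is that what the article does state, a 250 m trigger and a per-bout comparator, attenuates the response if applied as written.
- **The consequences are bounded.** The period-level ANOVA does not use the label. The 10% chance of prompting in contexts judged non-receptive limits permanent suppression, although labels from those prompts would carry the same bias.

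**Conclusion.** The concern holds in conditional form. If bouts are recorded whole, the comparison described attenuates the walk-faster response: a true 10% gain appears as about +1.5% at 300 m, rising to +7.3% at 1000 m. That rests only on the stated trigger and a steady speed before and after it. With any bout-to-bout noise or a success margin, labels are biased toward failure, most for short walks. The size is uncertain: under the assumed 10% gain and 10% SD, the loss in success rate at 300 m is between about 10 and 28 percentage points depending on how noisy short segments are. If recording starts at 250 m, the problem does not arise. It concerns the training label and a secondary analysis, not the period-level comparison of walking and stationary behavior.

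**What to change.** State whether recording covers the whole bout or starts at 250 m. Define walk-faster success as speed after the 250 m point compared with post-250 m speed in observation-period bouts in the same context. Use unrounded speed, and leave very short remainders unlabelled.

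For this study, apply the rule in the secondary analysis of prompt success wherever the 250 m time is stored or recoverable, for observation-period bouts as well as prompted ones. Where it is not, report the success rate as attenuated. Policies already trained and queries already sent cannot be changed. For the planned randomized trial, build the rule into the label and store the 250 m time for every bout.

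The cost is one time stamp per bout and a changed formula. The downside is noisier speed over short remainders and some bouts without a label.
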